
### Recruitment

#### Participant identification and stage 1 consent procedures

Potential participants will be identified by their usual care team at routine breast screening attendance and handed a stage 1 information leaflet at the time of their mammogram.

Advertising for the study will be present in screening clinic waiting areas in the form of posters and/or postcards. An information video will be available on the FAST MRI website, with a link/QR code to the video prominent on all advertising materials and will be shared via social media (including but not limited to Facebook and X).

Clients who wish to consent to stage 1 (consent to be screened for eligibility) can complete a consent form (paper or electronic version by following a link or QR code) and submit to the research team. Online supplemental material file 1 details both the stage 1 consent form and the stage 2 consent form.

#### Participant eligibility and stage 2 consent procedures

The research team will review the breast screening record (National Breast Screening System; NBSS) of potential participants consenting to stage 1 to check if the mammogram has been reported by the screening service and if they are aged (49 years+8 months) ≤ (53 years – 1 day). Interrogation of NBSS will be facilitated by bespoke software (created by the Scientific Computing Department of the Royal Surrey NHS Foundation Trust (RSNFT)).

Mammograms of participants who have consented to stage 1 will be measured for mammographic density, using an automated tool developed by RSNFT and results relayed to the research teams.

Participants who have been recalled by the standard mammographic screening process for further investigations but are otherwise eligible will be notified that they are not eligible to have a FAST MRI but are still eligible for data linkage. Participants who are ineligible for any other reason will be contacted and the reason for ineligibility will be explained.

Participants who are breast density B and remain potentially eligible will be identified and sent the stage 2 study information. The remaining inclusion and exclusion criteria will be confirmed with the participant during the stage 2 Informed Consent procedure.

Eligible participants consenting to stage 2 will be booked for a FAST MRI appointment.

The study flow chart is reproduced in Figure 1.

**Figure 1 F1:**
[figure not shown]
Study flow chart. FAST MRI, First post-contrAst SubtracTed MRI; NHSBSP, NHS Breast Screening Programme.

#### Intervention

The study intervention is a FAST MRI scan (**F**irst post-contr**A**st **S**ubtrac**T**ed images of a dynamic contrast-enhanced breast MRI scan).^11^ All standard MRI safety protocols will be followed, including the completion of a safety checklist to ensure that there are no MRI contraindications.

#### Scanning protocol parameters

The scanning protocol parameters will be within those set out for the DCE-MRI sequences of standard breast MRI by the NHSBSP as technical guidance for screening women at very high risk of breast cancer with MRI.^14^ The exact parameters used will be determined for each make and model of scanner (3T or 1.5T) by DYAMOND’s Central Quality Assurance Team during site set-up.

#### Quality assurance (QA) of FAST MRI scans

Dedicated FAST MRI QA phantoms (test objects)^29^ and an MRI equipment QA protocol have been developed for the DYAMOND study (to be published as a separate paper) for the purpose of optimising and standardising the FAST MRI scanning protocols and performing QA of the clinical FAST MRI scans at all study sites. All sites and scanners must pass the QA phase prior to greenlight for recruitment to the main study. This process enables quality checking of images and data centrally by the study QA Team.

#### FAST MRI interpretation and display

FAST MRI scans acquired during the study are displayed as maximum intensity projections and stacks of slices in axial and sagittal planes.

FAST MRI readers are both researchers and study participants (FAST MRI reader substudy).

DYAMOND FAST MRI readers must:

Be employed by a participating site.Be a mammogram reader for the NHS Breast Screening Programme.Have completed FAST MRI DYAMOND reader training.^30^,^34^Have credentialed (by interpreting a standardised assessment test set of FAST MRI scans with known outcome and achieving a predefined specificity and sensitivity).^34 35^Have completed Good Clinical Practice (GCP) training and be included on the site delegation log.Be able and willing to provide their informed consent.

FAST MRI readers are trained to classify scans according to the UK 5-point scale^14 36^ (MRI 1: normal; MRI 2: benign; MRI 3: indeterminate/probably benign; MRI 4: suspicious of malignancy; and MRI 5: highly suspicious of malignancy).

The FAST MRI scans will be interpreted by at least two certified FAST MRI DYAMOND readers, with arbitration for disagreement between readers.

The readers will be from a site other than that of the participant whose scan is being interpreted to ensure that they have no access to the participant’s standard care mammogram when interpreting the FAST MRI. This will be achieved using image viewing technology developed by RSNFT (RiViewer).^37^

All MRI 3 results will be reviewed by an expert panel who will additionally classify the scan as 3a or 3b.

#### FAST MRI results

If a participant’s FAST MRI scan is classified as:

MRI 1 or 2,^36^ the participant and her General Practitioner (GP) will be sent a normal findings confirmation letter.MRI 3a, the participant and GP will be sent a letter telling them that they will be invited for a repeat FAST MRI in 1 year (Y1 FAST MRI scan).MRI 3b, 4 or 5,^36^ the research team will contact the participant by telephone to inform them of an appointment for further investigation.Those found to have a biopsy-confirmed breast cancer (invasive and non-invasive) will be treated as per local practice appropriate for the size, stage and type of cancer detected.Those with no cancer confirmed will be invited for a repeat FAST MRI in 1 year (Y1 FAST MRI scan).

At year 1, scans will be classified into MRI 1/2 (no further action required) or MRI 4/5 with a referral to the assessment clinic. Readers at year 1 will have access to the year 0 scans for reference/comparison.

### Study outcomes, statistical analysis, data collection and data storage

#### Study outcomes

The primary outcome is the number of cancers (invasive and non-invasive) that are detected on FAST MRI, for participants whose FAST MRI scans were classified as MRI 3b, 4 or 5, after a negative mammogram.

Secondary outcomes are as follows:

The characteristics of the cancers detected by FAST MRI (including type, grade, size, stage, nodal involvement).Acceptability of the intervention through questionnaire and an additional qualitative interview of a subset of participants.Recruitment rate: Those that are recruited out of all those with density B and a clear mammogram that were contacted.Retention/compliance rate accounts for the number that withdraw from the study once recruited or do not attend the FAST MRI scan.Recall rate: The proportion of participants classified with a MRI 3b, 4 or 5 and invited for further investigation out of the total number of recruited participants who had a FAST MRI.Biopsy rate: The number of biopsies undertaken out of all participants recruited who had a FAST MRI.Early call rate: The number of participants who have a FAST MRI at Y1 (includes all those classified as MRI 3a, and those classified as MRI 3b, 4 and 5 who did not have cancer confirmed at Y0 biopsy) out of all participants recruited who had a FAST MRI at Y0.Adverse reactions to FAST MRI.Proportion of screening clients in each density category (A, B, C, D) of those screening clients consenting at stage 1.Interval cancers detected during the study period.FAST MRI classifications of Y1 scans (for all those with MRI 3a at Y0 and those with MRI 3b, 4 and 5 and no cancer detected at Y0).FAST MRI reader data, diagnostic accuracy of readers within the study (individually and by reader group and NHS site), numbers of scans requiring arbitration, standard arbitration outcomes and expert panel arbitration outcomes.

Cancer registry and NBSS records will be reviewed during the study to identify screen-detected or interval cancer data for all those taking part in the study including the data link participants (screening clients who consented at stage 1 with BI-RADS B mammographic density but did not have a FAST MRI scan for any reason and have not opted out of data linkage). This review will help to identify cancers that were screen detected at standard care mammography and any interval cancers that occur during the study for the screening clients who consented at stage 1, including those who also consented at stage 2.

#### Analysis of feasibility and uptake

Analysis of activity timings and comparison with the trial assessment schedule will provide insight into capacity with regard to MRI scanning, breast radiology workforce and screening assessment clinic provision within the NHS.

#### Micro-costing exercise

Data will be collected for a micro-costing exercise to enable estimates of cost for the intervention and for assessment clinics, biopsies and breast cancer treatments.

### Statistical analysis

#### Sample size calculation

From previous studies, in population-risk screening clients aged 50–54 of all mammographic densities having their first screening mammogram (prevalent round), standard mammography finds approximately 7.5 cancers per 1000 women screened^38^ (there are no reported figures specific to age 50–52). The addition of MRI may detect an additional 16.5 per 1000 women screened^20^ in women with mammographically dense breasts (density category D^24^). Meta-analyses have shown that sensitivities and specificities for FAST MRI did not differ significantly from those for DCE-MRI,^13 16^ but confidence in the evidence was low and FAST MRI may not pick up as many cancers as DCE-MRI.^9^

A Fleming’s two-stage design^39^ will be used to assess the number of additional cancers detected by FAST MRI. This design allows for early stopping after stage one, which would save patients, funding costs and time continuing to the end of the study if the question could be answered earlier. Based on previous research and consensus from radiologists, health economists and public and patient involvement (PPI) representatives, 4 additional cancers detected per 1000 women screened was deemed the minimum that would be required to be detected to warrant further investigation of this study population in a phase III trial. Setting the lower limit for the cancer detection at 0.004 (4 additional cancers detected per 1000 women screened), the target rate at 0.011, 80% power and a 5% one-sided significance level, then a minimum of 959 participants would be required (381 participants at the first stage). Thus, recruiting 1000 participants to the study will allow for 4% dropouts.

An interim analysis will be performed when 381 participants have been recruited. If one or no additional cancers are detected, the study may be halted for futility. If five or more cancers are detected, then the study may be stopped early as it has already been shown that the inclusion of this population in a phase III trial is warranted. Otherwise, the study will continue, and eight or more additional cancers are required to be detected by the end of the study to warrant inclusion of this population in a future phase III trial.

#### Data analysis plan

The primary outcome of the number of cancers detected on FAST MRI after a negative mammogram will be converted into a rate per thousand women screened to be comparable with current evidence and the associated 95% CI determined.

Summary statistics of the participant characteristics, tumour characteristics and adverse events will be presented as counts and percentages for categorical variables and means and SD or medians and IQRs for continuous variables depending on the distribution of the data.

The recruitment, compliance, recall, early call, biopsy and interval cancer rates, together with associated 95% CIs, will be determined.

This is a single-arm study, and therefore, no formal statistical testing is expected. All participants registered into the study will be analysed where possible. Cancer detection rates and adverse events will be analysed using the as treated population that had a FAST MRI. Participants who subsequently withdrew consent to participate will be analysed up until the point of withdrawal. To limit missing data, participants’ involvement is kept to a minimum with individuals only expected to attend for a FAST MRI and subsequent investigation depending on the result of the FAST MRI. Data collection is through the screening services and hospital data.

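### The plan disclaims formal testing although go/no-go rests on a one-sided 5% two-stage test, and its 95% interval can include the 4 per 1000 null at a marginal go

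*Protocol article*

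**What the plan says.** The Sample size calculation section of the protocol article sets out a formal test. "A Fleming’s two-stage design^39^ will be used to assess the number of additional cancers detected by FAST MRI". The null rate is fixed first: "Setting the lower limit for the cancer detection at 0.004 (4 additional cancers detected per 1000 women screened". The rest follows as "the target rate at 0.011, 80% power and a 5% one-sided significance level", and the result is "a minimum of 959 participants would be required (381 participants at the first stage". The boundaries are counts. At 381 participants, one cancer or none allows a futility stop and five or more allows an early positive stop. Otherwise eight or more in total are needed at the end for a go.

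The Data analysis plan section then states: "This is a single-arm study, and therefore, no formal statistical testing is expected". The primary count is to be "converted into a rate per thousand women screened to be comparable with current evidence and the associated 95% CI determined". It does not link that interval to the one-sided 5% level or to the two-stage stopping, and it names no interval method.

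**The concern.** A Fleming design is itself a single-arm hypothesis test, so having one arm is no reason to expect no test. As written, one section controls a type I error and the next says nothing is tested.

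The interval level adds to this. A two-sided 95% interval leaves 2.5% in the lower tail, while the decision rule spends 5% there. A result can therefore be a go under the rule while the published interval still contains 4 per 1000, the rate the rule was built to exclude. That would happen at a marginal go, where readers look hardest at the interval.

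The stopping rule also affects the estimate. A crude count divided by participants is not unbiased when the sample ends at 381 or 959 depending on the count. The Discussion says the results will inform the design of the future randomised trial, so an optimistic yield could carry forward.

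**Working it through.** **Inputs** (all from the Sample size calculation): p0 = 0.004; p1 = 0.011; n1 = 381; N = 959, so n2 = 959 − 381 = 578; stage 1 boundaries ≤1 and ≥5; final boundary ≥8.

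**1. Reproduce the design.** With X1 ~ Bin(381, p) and X2 ~ Bin(578, p),

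P(go) = P(X1 ≥ 5) + Σ over x = 2, 3, 4 of P(X1 = x) · P(X2 ≥ 8 − x).

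- At p = 0.004: 0.0195 + 0.2536×0.0303 + 0.1286×0.0848 + 0.0488×0.2028 = 0.048.
- At p = 0.011: 0.4086 + 0.1324×0.6111 + 0.1860×0.7616 + 0.1955×0.8794 = 0.803.

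The stated 5% one-sided level and 80% power are reproduced. The count rule is a valid test of 4 per 1000.

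**2. Compare the interval with the decision.** All figures are per 1000. The two-stage lower limit at a final total s solves P(early go, or stage 2 total ≥ s | p) = 0.025 for the 95% interval, or 0.05 for the 90% interval (the one-sided 95% bound).

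| Go result | Crude rate | Exact (Clopper-Pearson) 95% | Exact 90% lower | Wilson 95% lower | Two-stage 95% lower | Two-stage 90% lower |
|---|---|---|---|---|---|---|
| 5/381 | 13.12 | 4.27 to 30.36 | 5.18 | 5.62 | 4.27 | 5.18 |
| 8/959 | 8.34 | 3.61 to 16.37 | 4.16 | 4.23 | **3.46** | 4.04 |
| 9/959 | 9.38 | 4.30 to 17.74 | 4.90 | 4.95 | **3.84** | 4.50 |
| 10/959 | 10.43 | 5.01 to 19.09 | 5.67 | 5.67 | 4.09 | 4.83 |

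The unadjusted exact 95% interval includes 4 at 8/959 only. The two-stage 95% interval includes 4 at 8/959 and 9/959. Both 90% exact intervals exclude 4 at every go result in the table. Adjusting a 95% interval for the two stages does not remove the mismatch, because the level is the cause.

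**3. How often.** Probability of a go with exactly 8/959:

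- true rate 11 per 1000: 7.2% (9% of go decisions);
- true rate 8: 10.1% (21%);
- true rate 4: 1.8% (38%).

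**4. Bias of the crude rate, if both stops are followed.** Enumerating X1 and X2, the expected crude rate is 11.87 at a true 11 (+0.87), 8.12 at a true 8 (+0.12) and 3.32 at a true 4 (−0.68). An early go needs at least 5/381 = 13.1 per 1000. At a true 11 that stop has 41% probability, and the mean reported rate given that stop is 16.2.

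**5. Adjusted estimate.** The uniformly minimum variance unbiased estimator (UMVUE) at a stage 2 total s is

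Σ over x = 2, 3, 4 of C(380, x−1)·C(578, s−x), divided by Σ over x = 2, 3, 4 of C(381, x)·C(578, s−x).

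At s = 8 it is 7.94 against a crude 8.34; at s = 10 it is 8.44 against 10.43. After a stage 1 stop it equals x/381, the crude rate.

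**The case against.** **The interval method is not stated, and the analysis plan is not shown.** This stands. A reader might infer that the plan commits to an unadjusted interval that ignores the stopping rule, but the article does not say so, and choosing the method is normal content for the statistical analysis plan. What is fixed in the text is the 95% level and the no-testing sentence. Step 2 shows that an adjusted 95% interval would not cure the mismatch.

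**The decision uses counts, not the interval.** This also stands. A reader might infer that the go rule is invalid or could wrongly declare a go. The documents do not support that: the boundaries reproduce at alpha 0.048. Nor does the article claim that a go means the 95% interval excludes 4; it gives the rate a descriptive purpose.

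**The no-testing sentence may mean no comparative testing.** That is plausible given the reason offered, but the sentence makes no exception for the primary test.

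**The bias is small and conditional on the stops.** Overall it is under 1 per 1000 at both design rates, and both stops are worded as options. Part of the excess among go results is ordinary selection on success: at a true 11 the mean crude rate given any go is 13.6, but a single-stage study of 959 with the same cut-off of eight would average 12.0. The UMVUE does nothing for an early go, and even it averages 12.4 given any go.

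**The crude rate is not named as the planning value for the future trial.** Correct. The Discussion says only that the results will inform that trial's design and population.

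**Conclusion.** The point holds as a contradiction in the text and a mismatch of level, not as a fault in the decision rule. The Data analysis plan disclaims testing while the Sample size calculation fixes a one-sided 5% two-stage test. The 95% interval, taken as two-sided, can include 4 per 1000 on a go result. With an unadjusted exact interval that happens only at 8/959; with two-stage ordering, at 8/959 and 9/959; with Wilson, not at all.

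The effect on estimation is modest overall (+0.87 per 1000 at a true 11, −0.68 at a true 4). It is material only after an early go, where the reported rate cannot be below 13.1 per 1000.

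The figures assume analysis at exactly 381 and 959 participants. The bias figures also assume that both optional stops are followed. The correction is worth making because it is nearly free, but no boundary, sample size or go decision changes.

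**What to change.** 1. Replace the no-testing sentence with wording such as: no comparative testing is planned; the primary analysis is the two-stage one-sided 5% test defined in the sample size section.
2. Name the two-sided 90% exact interval built on the two-stage sample space (its lower limit is the one-sided 95% bound) as the interval tied to the decision. At 8/959 it is 4.04 to 15.32 per 1000. Keep the 95% interval, state its method, and label it descriptive.
3. Report the UMVUE beside the crude rate. It removes the unconditional bias if the stops are followed.
4. State that the UMVUE equals the crude rate at a stage 1 stop, so an early-go rate remains an overestimate and should be used for planning the randomised trial only with that caution.

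The cost is a few sentences and a few lines of code. The adjusted rate after a stage 2 go is lower than the crude one: slightly at the boundary (7.94 against 8.34 per 1000 at 8/959) and more at higher totals (8.44 against 10.43 at 10/959).

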### Data collection and storage

#### Main database at Warwick Clinical Trials Unit

Electronic case report forms for potential participants’ pseudonymised data once stage 1 consent is completed, to be held on a dedicated database hosted by Warwick Clinical Trials Unit on a secure server with restricted access. This data will include demographic data and also clinical and particularly breast history, risk factors for developing breast cancer (including Tyrer-Cuzick score) and menopause status.

#### Image database at Royal Surrey NHS Foundation Trust Scientific Computing Department (RSNFT)

Stage 1 participants’ pseudonymised mammograms (stage 1 consent completed)±FAST MRI scans (stage 2 consent completed) will be held on a dedicated image database hosted by the RSNFT.

Images are transferred via the Image Exchange Portal (IEP) to a FASTMRI node (hosted at RSNFT). The images are deidentified as they transition from IEP, meaning that no patient identifiable information is received outside the IEP network. On upload, a pseudonym will be assigned to the patient. This will be created by a lossful encoding algorithm and complex salt which will produce an encoded pseudonym that allows the linking of the screening client’s trial ID with the images.

The FAST MRI: DYAMOND data flow diagram is presented in Figure 2.

**Figure 2 F2:**
[figure not shown]
Data flow. FAST MRI, First post-contrAst SubtracTed MRI. (1) Clients use the eConsenting portals to consent to stage 1 and stage 2 of the trial. (2) Local; sites use the NBSS tool to produce a screening log. (3) Client’s images are acquired, and the local site registers the clients on the SMART web portal before transferring the images via IEP to the RSCH dedicated research node. (4) Images are received at the RSCH IEP node and processed through a pipeline to pseudonymise and prepare, then. (5) Images are pipelined and routed to the relevant staging areas. (6) Images arrive in a data management staging area in the dedicate cloud project. (7) Once images are processed by the data management staging area, they are routed to a temporary storage area (buckets). (8) A DICOM QR node exists in the dedicate cloud whose role is to monitor the incoming images into the temporary storage, and (9) Route the images to the Breast AI tool (10) Results from the Breast AI tool are routed to an output bucket (11) Results from the Breast AI tool are staged to the Data Management area (12) Results from the SciCom activities are routed to the Warwick database via dedicated APIs (13) The trial database is accessed by central DYAMOND research team and recruiting sites (14) Images are collected into reading sessions and staged in the RiViewer staging area. (15) Reading sessions are completed by various trial readers. (16) Results from reads are routed to the Data Management area and thence to the trial database. (17) SciCom team monitors these processes.

